## Abstract

**Introduction:**

Food intolerances are prevalent in Europe and can cause considerable physical discomfort, dietary restrictions and psychosocial challenges. Among the prominent causes of food intolerance are defects in the digestion and/or transport of short-chain fermentable carbohydrates, fermentable oligo-, di-, monosaccharides and polyols (FODMAPs). A common diagnostic tool for food intolerance is the hydrogen breath test, which monitors the production of H_2_ gas from the fermentation of ingested FODMAPs by colonic microbiota. However, this method is limited due to its relatively poor correlation with gastrointestinal (GI) symptoms experienced by patients. Diagnosis is complicated as food intolerance is often associated with functional GI disorders, while FODMAPs may exert their effects individually or in combination. Further research on the pathophysiology and the impact of intervention strategies for these conditions is required to improve the diagnosis of food intolerance.

**Methods and analyses:**

The Lactobreath pilot study is a randomised, two-arm, double-blinded controlled study. 120 healthy, free-living adults will undergo 6-hour postprandial tests with lactose or glucose (control) to investigate the molecular composition of human exhaled breath (exhalome) as a potential source of biomarkers associated with clinical and metabolic traits of lactose malabsorption (Lactobreath profiles). This serves as a proof-of-concept for the future application of this technology in diagnosing food intolerance. We will use a sensitive, non-invasive, real-time measurement technique based on secondary electrospray ionisation coupled with high-resolution mass spectrometry to analyse the chemical profile of the postprandial exhalome after lactose ingestion. Symptoms of lactose intolerance will be assessed using a standardised questionnaire and mechanistically linked to specific key metabolites of the discriminating breath profile. In parallel, a solid-state sensor will measure postprandial hydrogen gas in breath samples, while GI gases (CH_4_, H_2_, O_2_) and intestinal transit time will be monitored using a novel ingestible gas sensor (Atmo Gas capsule). Metabolites in urine, including lactose-derived metabolites, will be investigated using gas chromatography coupled with mass spectrometry. Postprandial bowel sounds will be recorded by wearable sensors (DigeHealth AG). Baseline assessments will be completed before the dietary challenge to capture usual dietary intake (repeated 24-hour recall), faecal microbiota (shallow shotgun sequencing) and to evaluate genetic polymorphisms using saliva samples (PCR analysis of selected penetrant single-nucleotide polymorphisms).

**Ethics and dissemination:**

The Lactobreath study has been approved by the Ethics Committee of the Canton of Zurich, Switzerland (#2023-01639). The project results will be published in open-access journals, presented at national and international conferences and communicated to the public and other relevant stakeholders via the communication channels of all investigators and partners. All results derived from the study will be accessible, in line with the Swiss National Science Foundation open access policy.

**Trial registration number:**

NCT06177938.

STRENGTHS AND LIMITATIONS OF THIS STUDYAdvancement of high-resolution metabolomics to explore the interface between food intake and human physiology through breath analysis.Controlled study design to limit variation in metabolite levels due to endogenous or external factors (eg, usual dietary intake, circadian rhythm, medications, cosmetics, exercise).Strict inclusion criteria and study demands may limit participant recruitment and retention.Metabolite identification is complex due to ambiguous ion assignments; this is addressed via a comprehensive annotation strategy using exhaled breath condensate collection, pathway analysis, standards and multiple analytical platforms.

## Introduction

 Food intolerance affects a significant proportion of the population, provoking gastrointestinal (GI) symptoms, including increased flatulence, abdominal pain, bloating and diarrhoea.^1^ Defects in the digestion and/or transport of short-chain fermentable carbohydrates, referred to as fermentable oligo-, di-, monosaccharides and polyols (FODMAPs), including lactose and fructose, are among the prominent causes of food intolerance. The pragmatic way to diagnose food intolerance is to confirm the absence of organic diseases or food allergies, before proceeding to the exclusion of FODMAPs from the diet of patients, followed by their controlled individual reintroduction.^1 2^ Diagnostic tests, such as the H_2_ breath test that monitors the production of hydrogen gas by the colonic microbiota fermenting the FODMAPs, have methodological limitations and do not consistently predict the GI symptoms experienced by the patients,^1^ reflecting the complexity of the mechanisms involved in food intolerance. Indeed, although the increased small intestinal water content due to the osmotic activity of the ingested carbohydrates is known to induce diarrhoea, and bacterial production of gases is a causal factor of flatulence and bloating, other factors can influence the GI symptoms associated with food intolerance, including colorectal transit time, the composition of the gut microbiota and immunologic phenomena.^2^ Interestingly, volatile compounds present in faecal water have been associated with GI symptoms of food intolerance.^3^ Furthermore, FODMAPs may exert their effect individually or in combination, further complicating food intolerance diagnosis and management. Managing food intolerances by low FODMAP diets is also complicated because the complete elimination of food sources of FODMAPs may induce nutritional deficiencies in patients. Reintroducing tolerated doses of the incriminating FODMAPs is, therefore, an integral part of the management of food intolerance.^4^,^7^

Research on the pathophysiological aspects of these conditions and the efficacy of intervention strategies is required to support the diagnosis and management of food intolerance.^6^ Furthermore, tests that can predict patients’ response to low FODMAP diets are also needed.

The Lactobreath study will investigate lactose intolerance (LI) in a proof-of-concept study to demonstrate the potential of exhaled breath as a source of biomarkers associated with food intolerance. LI describes the clinical symptoms resulting from lactose malabsorption (LM), the failure to digest and/or absorb lactose in the small intestine. In infants, the disaccharide lactose that is present in milk is cleaved in the small intestine by lactase, an enzyme encoded by the *LCT* gene, to produce galactose and glucose. However, lactase expression is epigenetically regulated and decreases during infancy in most humans.^8^ Polymorphic modifications associated with the development of pastoral activities approximately 8000–9000 years ago counter the epigenetic regulation of LCT so that about one-third of the human population now maintains an intestinal lactase activity into adulthood.^9^ Recent research has revealed that epigenetic regulation of lactase expression also occurs in lactase-persistent (LP) adults, explaining the decreased lactose-digestive ability observed with ageing.^8 9^ The consumption of lactose in the absence of intestinal lactase activity results in the lactose entering the colon, fermented by the resident microbiota, producing short-chain fatty acids (SCFAs) and gases such as H_2_, CH_4_ and CO_2_. The osmotic changes resulting from lactose in the colon, combined with these fermentation end-products, induce GI symptoms of LI, abdominal pain, bloating, flatulence, nausea and diarrhoea.

Various diagnostic approaches for assessing LM exist, including blood metabolite tests, breath measures, genetic tests and clinical presentation.^10^,^21^ While jejunal biopsies are considered the clinical gold standard for LM diagnosis, the lactose hydrogen breath test (LHBT) is the most widely used clinical diagnostic tool. The LHBT is based on measuring the H_2_ levels in the exhaled air of an individual for up to 5 hours postprandially after consumption of a specific dose of lactose. Diagnosis of LI is confirmed by the presence of H_2_, indicating that lactose has entered the large intestine and has been metabolised by the colonic microbiota, accompanied by GI symptoms. The available diagnostic tests are limited in their sensitivity and specificity, leading to frequent misdiagnosis and complicated by the presence of concurrent food intolerances. The medical domain has therefore moved to a clinically more relevant and inclusive approach by focusing diagnostic efforts on the GI symptoms of LI in the broader context of the FODMAPs.^1^ The Lactobreath study will focus on and investigate the potential of human exhaled breath as a source of biomarkers reporting on the clinical traits associated with LM, as a proof-of-concept for the diagnostic and dietary management of food intolerances.

Nutritional research has widely embraced metabolomic approaches to uncover the molecular complexity of foods and the consequent complexity of the response of organisms to food ingestion. Standard methodologies for monitoring the impact of food consumption on human metabolism, such as using food intake biomarkers combined with the measurement of validated clinical parameters, are often time-consuming or invasive, as they typically require human urine or blood analyses.^22^,^27^ In contrast, the analysis of exhaled breath presents an attractive alternative due to its non-invasive character, given the evidence for its high sensitivity demonstrated in extensive studies and applications over the last decades on various health-related issues.^2228^,^30^

Exhaled breath originates from the lungs and airways and contains a complex mixture of inorganic gases, traces of thousands of volatile organic compounds (VOCs) and microscopic aerosol particles.^31^,^38^ Both human breath VOCs and aerosol particles carry molecular information that comprises health and disease-related markers that can be used for medical diagnostic purposes. The number of clinical trials using breath analysis has experienced a steady rise over the last two decades,^39^ with wide applications in medical diagnostics, therapeutic monitoring and toxicology/precision medicine. Similar to blood, the composition of the exhaled breath in response to nutrition and dietary intake results from the metabolism of nutrients in the GI tract, the liver and the other body organs. This offers a unique opportunity to assess and understand the differences in individual responses to the same diet.

Recent advances in chemical sensing tools^40^,^43^ have facilitated the analysis, screening and decoding of volatile metabolites produced by the complex biochemical processes that evolve continuously within the human body. Existing mainstream technologies for the analysis of exhaled breath use either standalone or hyphenated mass spectrometry (MS) systems,^32 40^ ion mobility spectrometry,^44^,^48^ electronic noses^32^ and laser spectroscopy.^49 50^ Widely used off-line breath analysis techniques for VOCs and semi-VOCs include gas chromatography-mass spectrometry (GC-MS),^51^,^54^ GCxGC-MS^33^ and thermal desorption GC-MS,^55^ typically employing gas sampling bags, syringes or canisters. Proton transfer reaction MS,^56^,^61^ selected ion flow tube MS^61^,^65^ and membrane inlet MS^66 67^ serve for both online and offline analyses. Recently, high-resolution MS (Orbitrap, time-of-flight mass analysers^68^) coupled to ambient ionisation sources such as direct analysis in real-time,^69^ atmospheric pressure chemical ionisation^40^ and secondary electrospray ionisation (SESI)^70^,^78^ has been applied to measure human exhaled breath for disease diagnostic purposes in real-time. The development of real-time breath measurements offers a unique opportunity to assess the molecular breath signatures (exhalome) associated with the rapid onset of symptoms exhibited in food intolerance, a non-invasive strategy to gain insights into the specific metabolic response of individual consumers and offering a new route toward personalised nutrition.

The Lactobreath study uses state-of-the-art real-time breath metabolomics, suited for sensitive, non-invasive measurement of breath biomarkers in a controlled nutritional intervention that offers extensive and comprehensive participant characterisation for clinical and metabolic features relevant to lactose metabolism. A holistic approach is defined in the Lactobreath study to address and explore some of the challenges in the diagnosis of food intolerance by capturing metabolic processes and physiological variables that influence clinical phenotypes. Indeed, the Lactobreath breath profiles are focused on assessing clinical symptoms in the context of multiple existing diagnostic tools as well as physiological factors (eg, gut microbiota, GI transit) that are known to influence food intolerance symptoms. The Lactobreath study ultimately aims to support the development of a diagnostic test for LM and LI based on exhaled breath metabolomics, providing a non-invasive proxy for the subjective GI symptoms experienced by humans.

## Hypothesis and objectives

### Hypothesis

We hypothesise that lactose consumption generates different breath metabolomic profiles in people with lactose tolerance and those diagnosed with LI. These breath profiles are also expected to be associated with GI symptoms of LM.

The primary objective of the study is to identify postprandial metabolic profiles in human exhaled breath associated with GI symptoms of LM (Lactobreath profiles).

Secondary objectives:

To identify postprandial metabolic profiles in human exhaled breath reporting on the clinical traits associated with LM (Lactobreath profiles), including:▪ Genetic polymorphisms regulating the expression of the lactase gene.▪ Breath hydrogen.▪ Lactose-derived urinary metabolites.To mechanistically link Lactobreath profiles with metabolic traits associated with LM, including▪ Colonic gases measured by the Atmo Gas Capsule.▪ Urine metabolome.▪ Gut microbiota composition.To associate colonic gases and symptoms of LI with bowel sounds using a digital biosensor.

## Methods and analysis

### Study design

The study design is a randomised, two-arm, double-blinded intervention. The study set-up is a monocentric, national study. The study design allows the discovery of biomarkers that report on LM by comparing the breath response to lactose ingestion in three predefined groups defined by the characteristics of LM. The study began in June 2024, with an expected primary completion by the end of 2025.

The specificity of the candidate biomarkers to lactose exposure will be confirmed by the responses of the biomarker in the control condition (glucose solution). By randomising the participants to lactose or glucose intervention arms, the risk of bias due to unknown confounding factors is reduced. Furthermore, the participants will be blinded to the intervention type received to limit non-metabolic responses to dietary exposure. There is a risk that by using a parallel study design, some variation in the biomarkers that relate to the individual will be introduced; however, for the purpose of diagnostic testing, the biomarkers need to be highly specific and robust to variation between individuals. Consequently, the choice of design could help identify more discriminant biomarkers.

### Study population and eligibility

The study will be conducted in healthy adult men and women with or without the genetic ability to digest lactose. Participants will be enrolled according to inclusion and exclusion criteria based on those described by Ramakrishnan *et al*,^79^ ensuring the selection of participants with homogenous clinical profiles and avoiding pathologies that could confound the study results. Specifically, eligible adults (aged 18–65 years at screening) must reside in Switzerland, be English/German speakers and agree to refrain from all other treatments and products used for dairy intolerance (eg, Lactaid dietary supplements) during study involvement.

Study exclusion criteria include the following: milk allergy, pregnancy or lactation at time of enrolment, cigarette smoking or other use of tobacco or nicotine-containing products (<3 months of screening), diagnosis with disorders known to be associated with abnormal GI motility, history of surgery that alters normal GI tract function, suspected obscure GI bleeding, diabetes mellitus, HIV, hepatitis B or hepatitis C, body mass index >35 kg/m^2^, chronic antacid and/or proton pump inhibitor use, recent use of systemic antibiotics (<2 months of screening), history of alcohol and/or drug abuse (past 12 months), recent bowel preparation for endoscopic or radiologic investigation (<4 weeks of screening), severe irritable bowel syndrome (IBS) (ie, IBS Symptom Severity Score >400), dietary restrictions including vegan or vegetarian diet and enrolment in another clinical trial (<3 months). In addition, exclusion criteria for using the Atmo Gas Capsule are applied to minimise the risks associated with its use: presence of strictures (suspected or known), fistulas or any GI obstruction; gastroparesis; history of gastric bezoar; swallowing disorders or dysphagia to food or pills; presence of implantable or portable electromechanical medical devices (eg, pacemakers). All participants must provide informed, written consent for participation in the study. Non-completion of the study procedures is an exclusion criterion.

A total of 120 adult participants will be selected and distributed into three groups based on the results of a screening test to confirm their genetic LM profiles and response to the ingestion of 25 g of lactose (lactose solution) test:^17^

24 genetically LP subjects with no GI symptoms in response to the ingestion of lactose (group 1).24 genetically lactase-non-persistent (LNP) subjects with no GI symptoms in response to the ingestion of lactose (group 2).72 genetically LNP subjects with GI symptoms in response to lactose ingestion (group 3).

Participants confirmed as genetically LP but experiencing GI symptoms after ingesting lactose will be excluded, as factors other than primary hypolactasia likely explain their symptoms.

The groups are chosen to allow discrimination of metabolic signals that relate to the genetic and clinical phenotypes of LI. Group 3 intentionally comprises more individuals to allow for secondary analysis of the differences in symptom severity, which is often very variable. The groups are important to enable the detection of biomarkers sensitive to differences in symptoms of LI to be captured.

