## Discussion

The Lactobreath study uses state-of-the-art real-time breath metabolomics, suited for sensitive, non-invasive measurement of breath biomarkers in a controlled nutritional intervention that offers extensive and comprehensive participant characterisation for clinical and metabolic features relevant to lactose metabolism. The holistic approach defined in the Lactobreath study aims to address and explore some of the challenges in the diagnosis of food intolerance by capturing metabolic processes and physiological variables that influence clinical phenotypes. Indeed, the Lactobreath breath profiles focus on assessing clinical symptoms in the context of multiple existing diagnostic tools as well as physiological factors (eg, gut microbiota, GI transit) that are known to influence food intolerance symptoms.

In the clinical field, there is currently a gap in the accurate detection of exhaled breath biomarkers for medical diagnostic tests. The Lactobreath study, with the extensive clinical characterisation of the subjects, aims to support the development of a diagnostic test for LM and LI based on exhaled breath metabolomics, providing a proxy for the subjective GI symptoms experienced by humans. The Lactobreath study will serve as proof of concept to extend the use of breath metabolite profiles to the more holistic topic of the diagnosis of food intolerance and its dietary management with low FODMAP consumption.

Notably, the reproducibility of the findings in different populations will need to be confirmed in a second study. The priority in this study is to confirm the proof of principle that dietary response can be distinguished via breath biomarkers. In this context, selecting participants from a limited population sample is important to control other factors that could confound the findings (eg, ethnic group). Moreover, the specificity of discriminating biomarkers to LM will need to be confirmed in a patient setting with other GI disorders.

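### Non-severe IBS is eligible, and the group rules may concentrate it in group 3, where it could contribute to the symptom profile

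*Protocol article*

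**What the plan says.** All of the following is in the protocol article.

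- **Population.** Study population and eligibility opens with "The study will be conducted in healthy adult men and women with or without the genetic ability to digest lactose". It gives the purpose of the criteria as "ensuring the selection of participants with homogenous clinical profiles and avoiding pathologies that could confound the study results".
- **Exclusions applied to everyone.** These include milk allergy, "diagnosis with disorders known to be associated with abnormal GI motility, history of surgery that alters normal GI tract function", suspected bleeding, gastroparesis, strictures and "severe irritable bowel syndrome (IBS) (ie, IBS Symptom Severity Score >400".
- **Symptom-based exclusion, lactase-persistent (LP) people only.** "Participants confirmed as genetically LP but experiencing GI symptoms after ingesting lactose will be excluded, as factors other than primary hypolactasia likely explain their symptoms". Genetic and lactose tolerance screening repeats this.
- **Groups.** Group 1 is 24 LP people without symptoms after lactose. Group 2 is 24 lactase-non-persistent (LNP) people without symptoms. Group 3 is 72 LNP people with symptoms. Assignment rests on genotype and on symptoms after a home lactose drink; no control drink is described at screening.
- **Overlap acknowledged.** The Abstract says that "food intolerance is often associated with functional GI disorders" and that this complicates diagnosis.
- **Limitation stated.** The Discussion says that "the specificity of discriminating biomarkers to LM will need to be confirmed in a patient setting with other GI disorders".

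**The concern.** The article recognises functional gastrointestinal disorders as a complication and says that confounding pathologies are avoided. Its IBS criterion nevertheless leaves IBS scoring 400 or less eligible unless another exclusion applies.

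The group rules then treat such people unevenly. An LP person whose IBS produces symptoms after the drink is removed. An LNP person with the same symptoms enters group 3 without a further check on cause. Groups 1 and 2 are selected for absence of symptoms. If IBS makes a symptom report more likely, it will be commoner in group 3 than in either other group. Comparing group 2 with group 3 holds genotype constant but not IBS, so that contrast does not remove the problem.

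The primary objective is a breath profile of the symptoms of lactose malabsorption. The symptom models are supervised, so a breath feature that tracks IBS, or an IBS-related reaction, helps classification and can be retained as part of a Lactobreath profile.

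**Working it through.** **Stated counts.** 24 + 24 + 72 = 120. Glucose arm: 4 + 4 + 12 = 20. Lactose arm: 20 + 20 + 60 = 100. These reproduce. Group 3 v groups 1 and 2 is therefore 60 v 40 in the lactose arm and 12 v 8 in the glucose arm. Group 3 v group 2 is 60 v 20 and 12 v 4.

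**Assumptions.** The article gives no IBS frequency, so every rate below is assumed.

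**Step 1: does selection on symptoms enrich IBS?** Let p be the IBS frequency among screened LNP people, s1 the symptom rate with IBS and s0 the rate without.

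- IBS share of group 3 = p·s1 / [p·s1 + (1 − p)·s0]
- IBS share of group 2 = p(1 − s1) / [p(1 − s1) + (1 − p)(1 − s0)]

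With p = 0.10, s1 = 0.80 and s0 = 0.40:

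- Group 3: 0.08 / (0.08 + 0.36) = 0.182, about 13 of 72.
- Group 2: 0.02 / (0.02 + 0.54) = 0.036, about 1 of 24.

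Over p from 0.05 to 0.20 and symptom rates from 60% v 50% to 90% v 30%, the group 3 share runs from about 6% to 43%. Enrichment follows whenever s1 exceeds s0; its extent depends on the inputs.

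**Step 2: what would a pure IBS marker do?** Take a marker that is positive in IBS, negative otherwise and unrelated to lactose. With IBS rate q3 in group 3 and q12 in groups 1 and 2, its balanced accuracy for symptom group is (q3 + 1 − q12) / 2. The probability of significance is exact power for Fisher's test, two-sided 0.05. For group 3 v group 2, q12 is used for group 2.

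| Assumed q3 v q12 | Balanced accuracy | Lactose, 60 v 40 | Lactose, 60 v 20 | Glucose, 12 v 8 | Glucose, 12 v 4 |
|---|---|---|---|---|---|
| 10% v 3% | 0.535 | 0.172 | 0.008 | 0.001 | 0.002 |
| 20% v 5% | 0.575 | 0.565 | 0.229 | 0.013 | 0.001 |
| 30% v 5% | 0.625 | 0.909 | 0.661 | 0.081 | 0.002 |

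These figures are for one perfect marker, one unadjusted test and the full lactose arm. False discovery rate control over many features, an imperfect marker or removal of held-out participants from the lactose arm would lower them.

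**Step 3: do the planned checks catch it?**

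- *Glucose arm.* It addresses this kind of artefact, but at 12 v 8 it would show the difference with probability 0.001 to 0.081. It cannot reveal an IBS-specific reaction to lactose.
- *Held-out 20 participants.* They come from groups formed by the same rules, so a profile partly driven by IBS would tend to validate in them.
- *Test-day baseline symptoms.* They are taken at −30 and −10 min after three days of restricted diet. They record current state, not IBS status.

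**The case against.** The strongest case against the point has several parts.

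- **Many non-lactose causes are excluded in everyone.** A reader might infer that such causes are screened out only in LP people. The eligibility section does not support that: motility disorders, altering surgery, milk allergy, severe IBS and others are excluded whatever the genotype. Only the symptom-based rule is confined to LP people.
- **The design has a control and rich measurement.** Breath is sampled before the drink, diet and faecal microbiota are recorded, and transit is measured. Separate models cover breath hydrogen, genotype and urinary metabolites. This stands in part: a constant, non-lactose feature could be seen in the pre-drink samples. But the symptom models are described in terms of metabolite levels after lactose, and none of these measurements records IBS.
- **The Discussion already limits the claim.** It leaves specificity against other disorders to later work. It does not assert that no such disorder is present here, and should not be read that way. Nor does it say that non-severe IBS may be present.
- **Covariates and sensitivity analyses may be in a fuller plan that is not shown.** Agreed; their absence from a condensed article is not the finding. The finding is the conflict between the stated purpose of the criteria and the IBS rule, and the uneven selection, both fixed in this text.
- **An LNP person with mild IBS who reacts to lactose may truly be lactose intolerant.** Also agreed. It makes a mixed profile likelier than a pure IBS one.

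**Conclusion.** The point holds in a limited form. The article's description of the sample conflicts with its own IBS criterion. Its group rules can make non-severe IBS commoner in group 3 than in groups 1 and 2, including between the two LNP groups. The existing checks are relevant but weak against this.

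The size cannot be established from the documents. Under assumed IBS rates of 10% v 3% to 30% v 5%, the probability that a pure IBS marker reaches significance in the lactose arm (60 v 40) runs from about 0.17 to 0.91. At the low end the risk is small. Even at the high end the marker's balanced accuracy is only 0.625. A reader might conclude that the Lactobreath symptom profile will be an IBS profile; neither the text nor these figures support that. The supported conclusion is that IBS may contribute to the profile.

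**What to change.** Leave eligibility unchanged. Before the symptom models are run:

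1. Retain the IBS status and severity score used to apply the exclusion. The article does not say that the score is taken from every participant, so record it for all enrolled participants if this is not already done.
2. Report both by group.
3. Prespecify a sensitivity analysis that repeats the symptom models (group 3 v groups 1 and 2, and group 3 v group 2) without participants with IBS. Claim a lactose-malabsorption symptom profile only if performance is broadly maintained, and define that beforehand.
4. Show any model adjusted for the score only beside the unadjusted one. Lactose intolerance may itself raise a symptom-based score, so adjustment can remove real signal.
5. Reconcile the healthy-sample and confounding-pathology statements with the IBS criterion, and state in the Discussion that non-severe IBS may be present in this sample.

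The cost is wording, one sensitivity analysis and possibly one extra recorded item. The sensitivity run has a smaller symptomatic group: at an assumed 10% to 30% IBS, 60 × 0.10 = 6 to 60 × 0.30 = 18 group 3 lactose takers drop out, leaving 54 to 42. Some true lactose-intolerance cases may be removed with them, so the result should be read beside the main analysis.
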